### Participants

All the participants were ambulatory children with spastic unilateral or bilateral CP[2,21]. The inclusion criteria were: 1) age between 6 and 13 years; 2) able to accept and follow verbal instructions; 3) ability to walk independently indoors, with or without walking aids (Gross Motor Function Classification System [GMFCS][22] levels I – III); 4) able to participate in a group training program. Children were excluded if they had instable seizures, if they had received treatment for spasticity or surgical procedures up to 3 months (for botulinum toxin type A injections) to 6 months (for surgery) prior to the study (or planned in the study period); if any change in medication was expected during the study period; or if they suffered from other diseases that interfered with physical activity.

A paediatric physiatrist working in each school pre-selected the children, based on the inclusion and exclusion criteria. The parents of the children who met these criteria received written information about the study. Accordingly, the parents of each potential participant were contacted by a researcher who gave further oral explanation, and answered any questions, if necessary. Written informed consent was given by the parents, and all children who were over 12 years of age. After all the informed consents had been collected, randomization was performed per school. The children were randomly allocated according to three stratification variables: GMFCS level (I; II–III); age (youngest: 6–9 years; oldest 10–13 years), and gender (boy; girl). Families were notified by means of a letter of their child's allocation to the intervention group or the control group prior to the first baseline assessment.

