### Sample size

At least 42 children were required to detect a difference in improvement of 5% on the Gross Motor Function Measure (GMFM) between the intervention group and the control group, with a power of 0.8 and an alpha of 0.05. To allow for some drop-outs, we aimed to recruit at least 50 children (25 intervention, 25 control).

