### Outcome measures

The data were collected in each of the participating schools by two blinded, independent research assistants. One pre- (T0) and three post-training assessments were made (T 1/2: after 6 weeks of training, T1: at the end of the training, T2: 6 weeks after the end of the training). The T0, T1 and T2 assessments were scheduled during a two-week period and the T 1/2 assessment was scheduled during a one week period. Measurements of the height and weight of the children were obtained during each session, as well as the type of shoes they wore and the type of orthosis or walking aid they used.

The outcome measurements in this study include assessments of the body function and structure, and activity and participation at ICF level (see Figure 3). The primary outcomes were gross motor function and walking ability (activity level), and the secondary outcomes were muscle strength (body function and structure level), mobility (activity level) and sport activities (participation level). In addition, various personal characteristics were measured once at baseline, in order to control for possible age, gender and gross motor function differences, as well as for emotional or behavioural problems (measured with the Strength and Difficulties Questionnaire [SDQ][26]) and degree of sexual maturation (based on the Tanner score[27]).

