### Data-analyses

Student T-tests (continuous data, if normally distributed), Mann-Whitney tests (continuous data, if not normally distributed), and Chi-square tests (dichotomous and ordinal data) will be used to evaluate group differences at baseline. Differences in change from baseline between the intervention group and control group for the three post baseline assessments will be evaluated by means of generalized estimating equations (GEE) for longitudinal analysis[36]. GEE is appropriate for analyzing longitudinal data with hierarchically structured data and the advantage of GEE is that this method takes into account the dependency of repeated measures within the same person. To determine the effect of the strength training program, changes in the training group will be compared to the changes in the control group (interaction between group * time).

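### The effect is a difference in change from baseline, with no baseline value, school or stratification factor named in the model, although randomization was per school and stratified on three factors

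*Protocol article*

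**What the plan says.** All references are to the protocol article.

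- **Participants.** After consent, "randomization was performed per school". "The children were randomly allocated according to three stratification variables": GMFCS level (I against II–III), age (6–9 against 10–13 years) and gender. The Setting section gives three schools.
- **Outcome measures.** Personal characteristics were recorded once at baseline "in order to control for possible age, gender and gross motor function differences", together with behavioural problems and sexual maturation.
- **Data-analyses.** Change from baseline at the three later assessments is compared between groups by GEE, and "changes in the training group will be compared to the changes in the control group (interaction between group * time". The only dependency the section says GEE handles is that between repeated measures on one child. Separately, t, Mann-Whitney and chi-square tests "will be used to evaluate group differences at baseline".
- **Sample size.** "At least 42 children were required to detect a difference in improvement of 5% on the Gross Motor Function Measure (GMFM", "with a power of 0.8 and an alpha of 0.05". Also, "we aimed to recruit at least 50 children (25 intervention, 25 control".

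**The concern.** The analysis as described does not use what the design put in place. Allocation was restricted by school and by three factors presumably chosen because they were expected to predict outcome, but none of them appears where the effect is defined. The baseline value enters only by subtraction, which is generally a less efficient use of it than regression on it. The stated intent to control for age, gender and gross motor function is not carried into the model that estimates the effect.

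With 42 children as the computed minimum and 51 recruited, there is little precision to spare. If the stratification factors predict change and are balanced by design, standard errors that ignore them are too large and the test is conservative.

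**Working it through.** **1. The plan's own figure.** The Sample size section gives a difference of 5, power 0.80, alpha 0.05 and 42 children, but no standard deviation. The 42 can therefore only be inverted, not reproduced. Assume two-sided testing and 21 per arm:

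- Normal approximation: SD = 5 × √(21/2) / (1.960 + 0.842) = 5.78, so d = 5/5.78 = 0.865.
- t test with 40 df: d = 0.886, so SD = 5/0.886 = 5.64.

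Either is the standard deviation of change that the plan implicitly assumed. Steps 2 and 3 use d = 0.886.

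**2. Change score against baseline adjustment.** Take one follow-up, equal variances s² at both times, and correlation r.

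- Variance of change: 2s²(1 − r).
- Variance after adjusting for baseline: s²(1 − r²).
- Ratio: (1 − r²) / [2(1 − r)] = (1 + r)/2.

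**3. Power at 42 children.** The proposed model adds T0 (1 df), school (2), GMFCS stratum (1), age (1) and gender (1), which is 6 df. Residual df fall from 42 − 2 = 40 to 34. Estimating the T0 slope inflates the variance by an expected 39/38. The effective standardized difference is 0.886 / √[(1 + r)/2 × 39/38]. Strata and school are taken to explain nothing further.

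| Assumed r | Variance ratio | Power, 40 df, no inflation | Power, 34 df, with inflation |
|---|---|---|---|
| change score | 1 | 0.80 | – |
| 0.95 | 0.975 | 0.81 | 0.80 (0.796) |
| 0.9 | 0.95 | 0.82 | 0.81 |
| 0.8 | 0.90 | 0.84 | 0.83 |
| 0.6 | 0.80 | 0.88 | 0.87 |

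The last column is the fair comparison.

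**4. Leaving out balanced strata and school.** Suppose these explain a share R² of the variance of change and are perfectly balanced. The unadjusted two-sided type I error is then 2 × [1 − Φ(1.96/√(1 − R²))]. Power below uses the normal approximation (d = 0.865), with no charge for degrees of freedom.

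| Assumed R² | Type I error, unadjusted | Power, unadjusted | Power, adjusted |
|---|---|---|---|
| 0.05 | 0.044 | 0.81 | 0.82 |
| 0.10 | 0.039 | 0.81 | 0.84 |
| 0.20 | 0.028 | 0.83 | 0.88 |

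**5. Why main effects and not cells.** Fully crossed within school, the factors make 3 × 2 × 2 × 2 = 24 cells. For 51 children that is 51/24 = 2.1 per cell, too few to fit. The Participants section does not state the allocation method, so full crossing is itself an assumption.

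**The case against.** **Silence is not exclusion.** The Data-analyses section identifies the effect term and does not claim to list every model term. The Outcome measures section states an intent to control for age, gender and gross motor function, and a condensed article may leave the covariate list to a fuller document. This stands against any claim that covariates were ruled out. It does not dispose of the point, because the use of change from baseline is a stated choice. Whether T0 is one of the repeated outcomes or is subtracted from each later value, it is not a covariate. Exact equality with a simple change-score comparison would need T0 in the outcome vector, a saturated mean and complete data, so that is not claimed here.

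**The analysis is valid and matches the sample size.** The trial was powered on a difference in improvement, and that is what is analysed. It is unbiased under randomization, and ignoring balanced strata errs on the conservative side. This stands.

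**The gain is small and rests on assumed values.** This also stands. No correlation or standard deviation is given, and for an outcome with very high r the benefit from T0 vanishes once the extra parameters are paid for. The case for the strata and school depends on how prognostic and how well balanced they are. The less balanced they are, the less conservative the unadjusted test.

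**A stronger reading that the documents do not support.** A reader might infer that covariates will be chosen by the baseline significance tests, because tests are planned in one section and control for possible differences is mentioned in another. The Data-analyses section attaches no consequence to those tests, and the Outcome measures section mentions no test. A criticism of data-driven covariate selection therefore has no basis here.

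**Conclusion.** The point holds as one of precision and consistency with the design, not of validity. The stated effect model does not reflect the stated randomization, and the intended control for age, gender and gross motor function is not connected to it.

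The size is modest. At 42 children, power rises from 0.80 to about 0.81, 0.83 or 0.87 for r of 0.9, 0.8 or 0.6, with essentially nothing gained from T0 at r = 0.95. If strata and school explained 10% or 20% of the variance of change, adjusted power would be 0.84 against 0.81, or 0.88 against 0.83, before charging degrees of freedom. These figures assume two-sided testing, 21 per arm, one follow-up with equal variances, and values of r and R² that the document does not supply. Primary outcomes other than the GMFM may have a lower r and would then gain more.

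**What to change.** State one GEE model for each outcome. The post-baseline values are the response. The T0 value, school, GMFCS stratum (I; II–III), age and gender enter as prespecified main effects, not as 24 cells, together with group, categorical time and group × time. With T0 moved to the covariates, the effect at each assessment is the adjusted group difference at that assessment, not the interaction coefficient alone, and the text should say so.

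State in the same section that this is how the control for age, gender and gross motor function announced under Outcome measures is carried out. Replace the baseline significance tests with descriptive reporting by group. In a randomized comparison they test a null hypothesis that allocation already makes true.

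The cost is about six degrees of freedom and a change to the analysis wording. School, the stratification variables and T0 are already collected.

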## Discussion

Randomized clinical trials are considered to present the highest level of evidence. However, until now, only three randomized trials have evaluated the effects of a PRE functional strength training program in children with CP. These studies have reported positive training effects, although their results are still not truly convincing with regard to their corresponding outcome measures. This might be due not only to a difference in the evaluation methods that were applied but also to a difference in training characteristics. The majority of studies do not present a detailed report on their training program. Not only does this hamper correct interpretation of the results, but it also hampers implementation of the intervention in clinical practise in clinical practice. So, for a correct interpretation of the effectiveness of an intervention, standardization and reporting on all relevant aspects of the training protocol is of utmost importance.

For PRE strength training in particular, every study should give a detailed description of the key principle of the PRE: the timely progression in strength intensity, based on the child's *individual *level of strength, to ensure the principle of progressive overload[17,18]. To guarantee overload based on the individual level of strength, it should preferably be assessed according to the Repetition Maximum (RM).

Furthermore, each intervention study should also standardize and describe other relevant aspects such as frequency, duration and weekly volume of the training, and also the type and technique of each of the exercises.

Nevertheless, children with CP may present with a variety of motor disorders (e.g. poor co-ordination, loss of selective motor control), orthopaedic problems and other associated conditions (e.g. disturbances of cognition)[2], which often makes individual adjustments in the performance of the exercises necessary. Despite this, individual standardization of the training *should *and *can *be applied, in order to meet the requirements of progressive overload.

This paper outlines the design and all relevant aspects of the training protocol of a randomized controlled trial examining the effects of a school and group-based functional strength training program for children with CP. Our study was based on the hypothesis that an individualized, but group and school-based, functional PRE training will strengthen the lower limbs, and will accordingly lead to functional improvements in gross motor function and walking ability in children with CP. The results of this trial will be presented as soon as they become available.
